### Exclusion criteria

Criteria for exclusion are as following: pre-existing psychological disorders will be excluded; severe visual and/or hearing problems (impede the operation of RehaCom cognitive training system); Inability to follow instructions(impede cognitive training or assessment); Pregnant and lactating women (it is still unclear whether acupuncture will lead to abortion or other side effects); Bleeding disorder (the acupuncture procedure involves penetration of the skin, therefore we will exclude participants with thrombocytopenia, and so on); Serious illnesses of the heart, liver, or kidney, or other severe diseases (there may be risks that acupuncture induces stress action and thus harms patients with serious illness); Participating in other clinical trials that would affect the evaluation results of this study.

### Randomization and allocation

The random allocation sequence will be produced by an independent statistician via the PLAN sentences of the statistical software SAS9.1, who works in the Evidence-Based Center of the university and is not involved in the study. The eligible patients will be randomly and blindly allocated to the study groups (EG1, EG2, EG3, CG) to ensure internal validity of results according to 1:1:1:1(equal proportion rule). The random allocation sequence will be managed by a specified research assistant (RA) who is not involved in this trial and be concealed to the screeners and assessors until the last outcome assessment of the patient has been performed. The treating therapists (acupuncturist) will be notified of the allocation and arrange directly with the patient for the allocated treatment to be given. The eligible participants will be informed which group they are in by the project manager.

### Blinding

Blinding of study personnel in research projects is a main quality criterion of a study [43]. Nevertheless, blinding of therapists in an intervention study who perform experimental treatment in patients is not always feasible, especially if experimental intervention shall be combined with in the therapy. Consequently, hiding the patient’s allocation in this setting will not be possible. Therefore, neither therapists nor patients will be blinded in this study. We will assign a specified RA to be in charge of the management of the random allocation sequence and blind code of allocation in which the intervention group (CG, EG1, EG2, EG3) will be replaced by the alphabet A, B, C or D. In this trial, we will assign each investigators a well-defined obligation: the research assistant and treating therapists (acupuncturist) will be not involve in the assessment of outcomes; The outcome assessors and the statistic analyzer will be not involved in the participants’ screening and allocating. The blind code will be disclosed after the statistical analysis is completed.

### Treatment allocation

The intervention period in this trial will conduct at a frequency of 30 min per day (Monday to Friday every week), 12 weeks in total. Precise documentation of therapy/treatments, medication and the related lifestyle influence factors will be recorded in the case report forms (CRFs). The groups and intervention allocation listed in Table 2.

**Table 2 Tab2:** **Groups and intervention allocation**

Groups	Interventions
Control group(CG)	Conventional treatment
RehaCom training(EG1)	Conventional treatment + RehaCom cognitive training
Acupuncture group(EG2)	Conventional treatment + acupuncture treatment
Combination group(EG3)	Conventional treatment + acupuncture treatment + RehaCom training

### Conventional treatment

#### Basic treatment

The participants in the all groups will receive basic treatments which are usually delivered in Rehabilitation hospitals Affiliated to FJTCM. The doctor in charged will decide what the treatment or should be according to the ‘*Chinese prevention and treatment guidelines of cerebrovascular disease*’ [44]. This means that these patients will receive the treatment that the doctor considers to be the most necessary treatment includes conventional treatment of internal medication and multidisciplinary treatment which includes physiotherapy, occupational therapy, medical exercise therapy, hydrotherapy etc., except cognitive training. There are no restrictions for this condition and we will track the types of interventions provided and precise documentation of therapy treatments, medication, and therapy time/day.

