As a result, complementary or alternative therapies, such as acupuncture, are attractive to both patients and practitioners. Acupuncture, a core component of Traditional Chinese Medicine (TCM), has been used for thousands of years in several oriental countries to treat various diseases, with virtually no side effects in competent hands. A number of studies [15–21] demonstrated that acupuncture techniques may be effective for improving intelligence, stimulating consciousness and enhancing memory. These effects may result from activation and/or stimulation by acupuncture of the regions responsible for cognition. In the system of TCM, Baihui (DU 20) and Shenting (DU24) are acupoints that belong to the Du Meridian and may be important in the nervous system. Acupoint Shenting (DU24) is considered to be involved in the improvement of human health and spirits, and Baihui (DU20) in the adjustment of memory function. Therefore, the Baihui and Shenting acupoints are commonly used in China to clinically treat post-stroke cognitive impairment [22, 23]. A series of experimental studies have demonstrated that acupuncture can improve cognitive function through: 1. regulating the aging related changes in gene profile expression of the hippocampus [24]; 2. preventing oxidative stress [25]; 3.regulating the expression of apoptosis related genes in hippocampus [26, 27].

Cognitive rehabilitation (CR) is a mechanism that can compensate for an impaired nervous system by systematic treatment that can cause functional changes through the reinforcement, promotion and relearning of previously learned or new patterns to enhance cognitive function [28]. At present, cognitive training mainly includes traditional cognitive retraining and computer-assisted cognitive training, e.g. [29]. Computer-assisted cognitive training allows automation of many cognitive training procedures, making it possible to meet demand for care, improve stimulation quality, increase patient record reliability and optimize performance in impaired functions [30, 31].

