As mentioned above, the acupuncture focus on the global cognitive function from the holistic conception of TCM, while the RehaCom cognitive training concerns the specific impaired cognitive functions which need to be trained from the viewpoint of symptomatic treatment. However, the cognitive impairment after stroke is so complexity that one single treatment cannot resolve effectively. Due to the limited efficacy of the interventions separately used and the growing interest in recovery from post-stroke cognitive dysfunction has led to development of multiple therapeutic strategies for cognitive rehabilitation, that is, the remediation or alleviation of cognitive deficits resulting from neurological damage [36]. As the two interventions which can treat the cognitive impairment from global cognitive function to specific impaired cognitive function, we firmly believe that the interaction of multiple therapeutic strategies (the combination of acupuncture and RehaCom cognitive training) to produce an effect greater than simply the sum of the individual effects of each intervention if they were used separately. Besides, the effects of acupuncture and RehaCom cognitive training have not been systematically compared, nor has the possibility of a synergistic effect of combination of the two therapeutic modalities been evaluated.

Nonetheless, after reviewing a great amount of literature, we found that few studies had addressed these questions. So it is still unclear whether this form of intervention (acupuncture combined with RehaCom cognitive training) can be considered as a treatment of choice. Though, a current systematic review [37] showed that acupuncture in combination with other therapies could significantly improve cognitive functions. Besides, acupuncture would be a useful tool in conjunction with RehaCom from our preliminary clinical practice. However, convincing evidence is still inadequate. Therefore, we designed a randomized controlled trial of 2 × 2 factorial design to address these problems and hopefully provide a more conclusive answer to the questions. We hypothesized that the synergistic effect of acupuncture and RehaCom cognitive training is greater than simply the sum of the individual effects of each intervention if they were used separately; and the acupuncture or RehaCom cognitive training significantly improves cognitive outcomes, or to a similar extent, assessed after the intervention, compared to the control group.

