In this trial, our first aim is to evaluate the synergistic effect of acupuncture and RehaCom cognitive training on cognitive dysfunction after stroke. Our second aim is to determine whether acupuncture and RehaCom cognitive training, alone or in combination, are more effective than conventional treatment on the rehabilitation of post-stroke cognitive dysfunction. The work reported in this article is financed by the Program of International S&T Cooperation (No. 2011DFG33240), Ministry of Science and Technology of the People’s Republic of China.

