## Method/Design

### Study design and setting

We propose a randomized controlled trial with 2 × 2 factorial design in which the two interventions (acupuncture and RehaCom training) are to be delivered to **four** groups defined by the presence or absence of each intervention, with one arm without both interventions as a control group. Patients were randomized to one of the four treatment arms: (i) Experimental Group1 (EG1): conventional treatment plus RehaCom cognitive training; (ii) Experimental Group 2 (EG2): conventional treatment plus acupuncture treatment; (iii) Experimental Group 3 (EG3): conventional treatment plus the combination of acupuncture and RehaCom cognitive training; and (iv) Control Group (CG): Conventional treatment alone. All groups receive the same intervention time of 30 minutes. The investigation will have an intervention period of 12 weeks and will be carried out in the Rehabilitation Hospital Affiliated to Fujian University of Traditional Chinese Medicine (FJTCM). Cognitive abilities screening instrument on cognition performance [includes mini-mental state examination (MMSE), Montreal cognitive assessment (MoCA), functional independence measure scale (FIM)] will be assessed in all groups before and after randomization (at 0,4,8 and 12 weeks). The flow diagram for this trial is presented in Figure 1.

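### The background-care rule keeps cognitive training out of usual care in every arm but sets no such limit on acupuncture, the other factor of the 2 × 2 design

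*Protocol article*

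**What the plan says.** The protocol article, Basic treatment, sets one rule on background care for all four arms. Patients receive "basic treatments which are usually delivered in Rehabilitation hospitals Affiliated to FJTCM". The doctor in charge decides, by reference to a cited Chinese guideline on cerebrovascular disease, and patients get "the treatment that the doctor considers to be the most necessary treatment". The content is internal medication and "multidisciplinary treatment which includes physiotherapy, occupational therapy, medical exercise therapy, hydrotherapy etc., except cognitive training. There are no restrictions for this condition". The treatments given and the therapy time per day are then tracked.

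Study design and setting defines the four arms by presence or absence of acupuncture and RehaCom, "with one arm without both interventions as a control group". Table 2 lists acupuncture for EG2 and the combination arm (EG3) only.

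The Background states that "the Baihui and Shenting acupoints are commonly used in China to clinically treat post-stroke cognitive impairment" and reports that "acupuncture would be a useful tool in conjunction with RehaCom from our preliminary clinical practice". Blinding says that neither patients nor therapists are blinded. Statistical analysis says that all allocated patients are analysed by intention to treat.

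**The concern.** A factorial trial has two factors to keep out of background care. The authors saw this need for one: they name cognitive training as an exception. The list of permitted therapies is open-ended, no other exception is named, and the next sentence says that nothing further is restricted. The exclusion criteria do not bar concurrent acupuncture either.

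Acupuncture given as usual care in CG or EG1 would bring those arms closer to EG2 and EG3. Because patients are analysed as allocated, the dilution would stay in the estimates. It would affect the acupuncture effect and also the interaction, which is the trial's first aim. It would also reach the second aim, whether the interventions, "alone or in combination, are more effective than conventional treatment", because the comparator itself would contain some acupuncture.

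**Working it through.** **Inputs** (Sample size section): planned MMSE improvements CG 2.7, EG1 5.9, EG2 3.7, EG3 6.0; SD 5.2; about 50 per group before dropout; α = 0.05; power 90%. The share c is not in the documents and is assumed to be 10–30%.

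**Plan's own figure.** The mean of the four values is 18.3/4 = 4.575. The sum of squared deviations is 3.516 + 1.756 + 0.766 + 2.031 = 8.07. The noncentrality needed for 90% power with 3 degrees of freedom is 14.17, so n = 14.17 × 5.2² / 8.07 ≈ 47.5, that is 48 per group. The exact noncentral F calculation gives 49. Both agree with about 50, so these means and this SD are the right base for the next step.

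**Planned contrasts without contamination**
- EG2 − CG = 3.7 − 2.7 = 1.0
- EG3 − EG1 = 6.0 − 5.9 = 0.1
- Factorial acupuncture effect = (1.0 + 0.1)/2 = 0.55
- Interaction = 0.1 − 1.0 = −0.9
- EG3 − CG = 3.3

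**With an equal share c of CG and EG1 needled at full effect.** CG′ = 2.7 + 1.0c and EG1′ = 5.9 + 0.1c, so the first four contrasts are each multiplied by (1 − c), and EG3 − CG′ = 3.3 − 1.0c.

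| c | EG2 − CG | EG3 − EG1 | Factorial effect | Interaction | EG3 − CG |
|---|---|---|---|---|---|
| 0 | 1.0 | 0.10 | 0.55 | −0.90 | 3.3 |
| 0.1 | 0.9 | 0.09 | 0.495 | −0.81 | 3.2 |
| 0.2 | 0.8 | 0.08 | 0.44 | −0.72 | 3.1 |
| 0.3 | 0.7 | 0.07 | 0.385 | −0.63 | 3.0 |

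**Scale at c = 0.3, n = 50 per arm**
- Two arms: SE = 5.2 × √(2/50) = 1.04. EG2 − CG and EG3 − CG each shift by 0.3, and 0.3/1.04 = 0.29 SE.
- Factorial effect: SE = 5.2 × √(2/100) = 0.735. The shift is 0.165, and 0.165/0.735 = 0.22 SE.
- Interaction: SE = 5.2 × √(4/50) = 1.471. The shift is 0.27, and 0.27/1.471 = 0.18 SE.

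**Unequal shares.** With c0 in CG and c1 in EG1, the interaction is 0.1(1 − c1) − 1.0(1 − c0). For c0 = 0.3 and c1 = 0.1 it is 0.09 − 0.70 = −0.61. For c0 = 0.1 and c1 = 0.3 it is 0.07 − 0.90 = −0.83. Unequal uptake therefore does not change the order of magnitude.

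**The case against.** The arm definitions go some way to answer the point. CG is to have neither intervention, Table 2 places acupuncture on top of conventional treatment in two arms only, and the acupuncturist is told the allocation and arranges the allocated treatment. The doctor also works to a cited guideline. Its content is not available here, so it cannot be said that it admits acupuncture. The therapies actually listed do not include acupuncture; it could enter only through the open end of the list. The remark on common use of the acupoints concerns China in general, and the remark on clinical practice concerns acupuncture together with RehaCom. Neither describes this hospital's basic care.

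Much of this stands, and it limits the finding to a possibility. It does not remove it. The arm definitions say what the trial assigns; the Basic treatment section says what the doctor may add. If the arm definitions alone governed co-treatment, the exception for cognitive training would have been unnecessary.

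The size is also open to challenge. Holding power for a given effect would take 1/(1 − c)² times the sample, that is 1.23 at 10% and 2.04 at 30%, which sounds large. But on the planned means the power for EG2 against CG at 50 per arm is only 15.9% without contamination, and 11.7% at c = 0.2. The low power comes from the planned means and is a separate matter, so the multiplier should not be read as the weight of this point.

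A reader might infer two stronger things. One is that CG and EG1 patients are in fact receiving acupuncture; nothing in the article says so. The other is that the statement "All groups receive the same intervention time of 30 minutes" is false for CG, because no CG session is described. The article does not establish that. EG1's 30 minutes rests on the same general statements that cover CG, since the RehaCom section gives no session length. Quality control mentions a therapist in the control condition, and a condensed article may leave a control session undescribed. It is worth asking whether CG has a time-matched session, but that is a query and not part of this finding.

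**Conclusion.** The concern holds as a badly set rule: background care is expressly closed to one factor and left open to the other in an unblinded trial. The effect, if any, is dilution of the acupuncture and interaction contrasts by (1 − c). For c = 10–30%, the factorial acupuncture effect falls from 0.55 to 0.50–0.39 and the interaction moves from −0.9 to between −0.81 and −0.63. These shifts are small against sampling error. The figures rest on an assumed c, equal in CG and EG1, on off-protocol acupuncture working as well as the trial's own, and on the planned means. The case for acting is that the gap touches both aims and is nearly free to close, not that harm has been shown.

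**What to change.** 1. In Basic treatment, extend the existing exception to read: *except cognitive training and acupuncture outside the assigned arm, for the 12-week intervention period*.
2. Report any off-protocol acupuncture by arm. Basic treatment, Treatment allocation and Quality control already provide for recording all treatments, so no new data are needed.

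The cost is one changed phrase and one by-arm summary, with no change to the sample size. The downside is a small restriction on what the treating doctor may offer while recruitment is ongoing. Patients treated before the change would remain under the old rule, which the by-arm summary would make visible.

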#### Health education

The doctor in charged will base on the blueprint of ‘*Out of The Misunderstanding of the Rehabilitation of Stroke Patients*’ [45] (the first prize of Popular science books from the Chinese Association of TCM)to health education the patients to change their lifestyle and the concept on the rehabilitation of stroke. Two strategies will be used for health education: (1) Educational brochures on stroke, published by FJTCM, will be sent to participants. Information in these brochures will include the concept, epidemiology, etiology, common symptoms, diagnosis, treatments and precautions that should be taken. (2) The rehabilitation therapist will introduce and explain the contents of the educational brochures to all participants in person. The aim is to help participants learn about and understand stroke and to implement strategies to help alleviate the disease. The frequency (quantity) of related factors applied to the patients will be precisely documented in the CRFs.

### RehaCom cognitive training

The computer-based cognitive training program, Hasomed RehaCom (CE certified, EN-ISO-13485) is intended for patients with acquired cognitive deficits after brain damage, e.g. after a stroke [46]. The RehaCom [33] software has five different therapeutic groups aimed at restoration of attention, memory, executive functions, and visual field, respectively. The developer (International Cooperator-Reha Rheinfelden) has helped to provide a Chinese revised version of the software. The program contains several modules with different levels of difficulty, automatically increasing task difficulty level as the subject successfully executes simpler procedures. Recording of number of errors and test completion time for all patients and a training results file enable continuity over several sessions and database storage of results. The computer gives patients appropriate instructions and feedback on performance in their own language (in our patients Chinese). The following were the areas of training: divided attention, concentration, reaction (time), word memory, verbal memory (i.e., whole text, not just individual words), spatial memory and figure memory. Application of the training sessions can be learnt after a short instruction. This will also be part of the training workshop prior to commencement of the study. Patients’ training used RehaCom software for interactive computerized cognitive rehabilitation, a complete description of which has been published [47].

### Acupuncture protocol

For every treatment visit, participants are treated with 2 acupuncture points [Baihui (DU20)] and [Shenting (DU24)]. Patients will be treated by an experienced acupuncturist with a working experience of at least five years in neurological rehabilitation with acupuncture. The detail of acupoints showed in Table 3.

**Table 3 Tab3:** **Acupuncture points selected in this protocol**

Acupuncture points	Location
Baihui (DU20)	On the head, 5 *B-cun superior to the anterior hairline, on the anterior median line.
	Note 1: DU20 is located in the depression 1 *B-cun anterior to the midpoint of the line from the anterior hairline to the posterior hairline.
	Note 2: When the ears are folded, DU20 is located at the midpoint of the connecting line between the auricular apices.
Shenting (DU24)	On the head, 0.5 *B-cun superior to the anterior hairline, on the anterior median line.

*B-cun: Proportional bone cun. This method divides the height of the human body into 75 equal units. Using joints on the surface of the body as the primary landmarks, the length and width of every body part is measured by such proportions.

#### Definition of acupuncture

Acupuncture originated in ancient China approximately 2,500 years ago and is a key component of TCM. Acupuncture techniques involve insertion of needles and the stimulation of the needles may involve manual, electrical, heat, laser or other forms of stimulation [48].

#### Needling method

Points are first sterilized with alcohol, and then the doctor’ s left hand must fix the target position, the right hand insert the thin, disposable acupunctures needle (Huatuo, single use, φ0.35 × 40 mm, distributor Suzhou HuaTuo Medical Instruments, Suzhou, China) at angle of insertion 10° ~ 20°(between needle and scalp) to a depth of approximately 0.3-0.5B-cun. Following insertion, stimulation of the acupuncture point will be performed using of bidirectional rotation of the needle sleeve, to achieve the sensation known as *Deqi*, which is commonly described as a ‘glowing’ feeling. The needle will be maintained in place for 30 minutes, with bidirectional rotation of the needle sleeve (with amplitude and rotation speed as stipulated previously) for one minute, every 10 minutes (a total of four such rotations per session). Following the treatment session, the needles will be withdrawn.

### Acupuncture combined RehaCom cognitive training

For the combined group, patients will receive acupuncture needling and training with the RehaCom cognitive system while the needles inserted (at the same time).

